#### The KIDMED questionnaire

The KIDMED index was derived on the basis of a 16-item questionnaire administered separately from the 24-hour recalls as part of the enKID survey [9]. KIDMED was created to estimate adherence to the Mediterranean diet in children and young adults, based on the principles that sustain Mediterranean dietary patterns and those that undermine it. Items denoting lower adherence were assigned a value of -1 (4 items) and those related to higher adherence were scored +1 (12 items). Scores range from -4 to 12, with higher scores indicating greater adherence to the Mediterranean diet. A low adherence to the Mediterranean diet was defined as scoring below 6 points for the KIDMED index.

#### Eating behaviours

Eating behaviours were determined by the validated Dutch Eating Behaviour Questionnaire for Children (DEBQ-C) for use with Spanish children [10]. The DEBQ-C is a questionnaire adapted to age (7 to 12 years old), which assesses the presence of *External Eating*, *Emotional Eating*, and *Restrained Eating*. It is a self-applied questionnaire composed of 20 Likert type questions.

#### Physical activity assessment

Level of physical activity (PA) is assessed by the Physical Activity Questionnaire for Children (PAQ-C). The PAQ-C asks about different activities to define the PA level of the last week (the last 7 days) [11]. It provides a summary PA score derived from nine items. Each question is scored on a 5-point scale, with higher scores indicating higher levels of activity. The first question is a checklist of 22 common leisure and sports activities. The PAQ-C is widely accepted [13-15] and recommended [16] for international and national studies. In addition, a systematic review of measurement properties of self-report PA questionnaires for children concluded good to moderate validity and reliability of the PAQ-C [15]. The Physical Activity Questionnaire for Older Children (PAQ-C) and for Adolescents (PAQ-A) are self-administered, 7-day recall instruments, which were designed to provide a general estimate of PA levels in 8–20-year-old youth during the school year. Questionnaire items include weekly participation in different types of activities and sports (activity checklist), effort during physical education (PE), and activity during lunch, after school, evening and at the weekend.

#### Quality of life

Quality of life is assessed by the KIDSCREEN-10 questionnaire [12]. The KIDSCREEN-10 is a valid measurement tool of health related quality of life in children and adolescents. This questionnaire is the shortest version of three questionnaires (KIDSCREEN-52, KIDSCREEN-27, and KIDSCREEN-10). The KIDSCREEN-10 score contains 10 items. Each item is answered on a 5-point response scale. The KIDSCREEN- 10 Item statements are: (1) Have you felt fit and well? (2) Have you felt full of energy? (3) Have you felt sad? (4) Have you felt lonely? (5) Have you had enough time for yourself? (6) Have you been able to do the things that you want to do in your free time? (7) Have your parent(s) treated you fairly? (8) Have you had fun with your friends? (9) Have you got on well at school? (10) Have you been able to pay attention?

#### Sleep duration and quality

Parents answered to the questions of the Spanish version of the Pediatric sleep questionnaire (PSQ) to report on children’s sleep duration and quality [17]. The PSQ is a reliable measure for assessing SRBP in children, and has demonstrated valid results in a pediatric population compared with polysomnography (PSG) [18] The PSQ consists of 22 items and three subscales that examine snoring, daytime sleepiness, and daytime behavior. The PSQ scores are averaged so values range from 0 to 1 and are assessed as a continuous variable [18]. Parents were also asked to report the usual earliest and latest time their child went to bed and woke up for weekdays and weekends separately. Sleep duration was calculated as the number of hours on weekdays between the average of the usual earliest and latest bed time and the average of the earliest and latest times the child woke up.

### Data collection in parents

#### Dietary assessment

Diet quality is recorded by the short Diet Quality Screener (sDQS) [19]. Parents are asked to base their responses on their usual dietary behaviors over the previous 12 months, reporting their habitual intake of 18 food items grouped in 3 food categories.

#### Physical activity

The short version of the Minnesota Leisure-Time physical Activity Questionnaire (sMLTPA) is administered to estimate parents time spend in leisure physical activities. The sMLTPA consists of 5 questions on leisure physical activities that explain about 90% variability of all activities of the long version of the MLTPA.

#### Socioeconomic status

Is recorded by a standard questionnaire.

### Evaluation plan

The evaluation plan will be carried out during two scholar years. All variables will be collected in parents and children at the beginning of the 1^st^ scholar year and at the end of the 2^nd^ scholar year. An intermediate data collection at the beginning of the 2^nd^ scholar will be performed in children.

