### Subjects

Two thousand two hundred forty nine children aged 8 to 10 years (4^th^ and 5^th^ grade of elementary school) were recruited from 4 Catalan cities (Terrassa, Sant Boi de Llobregat, Molins de Rei, and Gavà) from September to November 2012. The Thao-Child Health Program was implemented in Terrassa y Sant Boi de Llobregat whereas Molins de Rei and Gavà serve as control cities.

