### Data collection in children

#### Anthropometric variables

Anthropometric measurements are assessed for each individual following standard protocol by trained personnel. Body weight, height, and waist circumferences were measured on the same day of the first interview with the subjects wearing a t-shirt and light trousers. The measurements are performed without shoes and using an electronic scale (SECA 813), to the nearest of 100 g, a portable SECA 213 stadiometer (to the nearest 1 mm), and a metric tape (to the nearest 1 mm). Using a flexible non-stretch tape measure, waist circumference was measured by trained interviewers in the narrowest zone between the lower costal rib and iliac crest, in the supine decubitus and horizontal positions. Measuring devices are systematically calibrated.

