### Statistic

Data clean-up will be performed to minimize errors. Linear multivariate mixed models will be fit to analyze differences in changes in quantitative variables between groups. Pre-post changes will be considered as the response variable, and participants’ (age, gender, etc.) and municipalities’ characteristics (group membership) will be included as fixed effects explanatory variables. Additionally, to account for the hierarchical structure of the data, municipalities (Terrassa, Sant Boi de Llobregat, Molins de Rei, and Gavà) will be added to the model as random effects factors.

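### The change-score model names no term for time between measurements, so any difference between arms in mean follow-up length would enter the programme effect

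*Protocol article*

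**What the plan says.** The Subjects section gives one recruitment window for all four towns together: "from September to November 2012". Under Anthropometric variables, weight, height and waist "were measured on the same day of the first interview". The Evaluation plan collects all variables "at the beginning of the 1^st^ scholar year and at the end of the 2^nd^ scholar year", and adds for children: "An intermediate data collection at the beginning of the 2^nd^ scholar will be performed in children".

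The Statistic section sets the response: "Pre-post changes will be considered as the response variable". The participant covariates are given as "age, gender, etc", next to group membership. The four municipalities "will be added to the model as random effects factors". Neither the interval between the two measurements nor the date of either one is named. The Discussion confirms two programme towns and two control towns.

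**The concern.** The sample size rests on raw BMI, which changes as children of this age grow. A raw change score therefore depends on how long each child was followed. If baseline visits were spread over the recruitment window, follow-up length varies between children. Variation of that kind within both arms only adds noise. A difference in mean follow-up between arms is another matter, because it shifts the group coefficient.

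The named model terms would not remove such a shift. Age describes how old a child is, not how long the child was followed. A random intercept for town does not take out a difference that lies along the same line as group. With two towns per arm, chance balance of visit dates cannot be relied on.

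**Working it through.** **Plan's own figure.** Inputs from Sample size calculation: difference 0.6 kg/m2, SD 4.43 kg/m2, two-sided alpha 0.05, power 80%, 20% loss.

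- n per group = 2 × (1.960 + 0.842)² × 4.43² / 0.6² = 856 after rounding up.
- 856 / 0.8 = 1070, as stated. The timing point does not affect this figure.

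**Size of a possible timing bias.** Formula: bias = natural BMI rise per year × difference between arms in mean follow-up (months) / 12. The documents give neither input, so both are assumptions.

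- *Difference in follow-up.* Suppose one arm's towns filled the first half of the September to November window, the other arm's towns filled the second half, and final visits took place at the same time in both arms. The half-windows centre on about 23 September and 7 November, 1.5 months apart. Total follow-up would be roughly 20 months if the final wave falls in June 2014.
- *Natural BMI rise.* Taken as 0.3 to 0.8 kg/m2 per year.
- Low end: 0.3 × 1.5 / 12 = 0.0375 kg/m2; 0.0375 / 0.6 = 6%.
- High end: 0.8 × 1.5 / 12 = 0.10 kg/m2; 0.10 / 0.6 = 17%.

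**Range over other assumptions**, with a rise of 0.3 to 1.0 kg/m2 per year:

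| Difference in mean follow-up | Bias (kg/m2) | Share of 0.6 |
|---|---|---|
| 0 months | 0 | 0% |
| 1 month | 0.025 to 0.083 | 4% to 14% |
| 2 months | 0.05 to 0.17 | 8% to 28% |
| 3 months (extreme) | 0.075 to 0.25 | 13% to 42% |

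**Against the planned precision.** On the plan's inputs the individual-level standard error is 4.43 × √(2/856) = 0.214 kg/m2. A bias of 0.0375 to 0.10 is 0.18 to 0.47 standard errors. With no programme effect, a nominal 5% test would then reject about 5.4% to 7.5% of the time. In the 3-month, 1.0 per year extreme it would reject about 21% of the time. These figures ignore clustering and use the SD of BMI. The documents give no SD of change, and a smaller one would make the same bias weigh more.

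**How easily two towns per arm could be unbalanced.** As an illustration only, suppose the towns were visited one after another in four equal slots of 0.75 months, with A and B the two arms. There are six possible orders:

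- ABBA and BAAB: difference in mean baseline date 0.
- ABAB and BABA: 0.75 months.
- AABB and BBAA: 1.5 months.

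Only two of the six orders balance exactly.

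**The case against.** The strongest reply is that the article shows no error. It states no visit order and no timing gap between arms. The recruitment window is pooled over four towns and fits parallel visiting just as well. It dates recruitment rather than measurement, and the first interview carries no date. The covariate list is left open, and a condensed article may leave visit windows and time adjustment to the full protocol or analysis plan. All of this stands, and it limits the point to a conditional one: the article names no adjustment, which is not the same as showing that none will be made.

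A reader might go further in three ways that the document does not support.

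- *That town visit order did bias the programme effect.* No order is reported.
- *That going from autumn to the end of a school year is itself a bias.* That schedule applies to both arms, so the common seasonal shift cancels in the comparison. Only a difference in timing between arms matters.
- *That PAQ-C was distorted by holiday days at the start of term.* The article describes the PAQ-C and its adolescent version as "self-administered, 7-day recall instruments, which were designed to provide a general estimate of PA levels in 8–20-year-old youth during the school year". It does not say when term began or on which days the PAQ-C was given, so this is conjecture.

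It is also fair to say that the 1.5-month scenario stacks several assumptions and that its effect on the error rate is modest. Nor can a covariate for elapsed time separate timing from group if the two are fully aligned across only four towns. That last objection is a reason to put scheduling ahead of modelling. It does not remove the exposure: a raw change score, a window of up to three months, two towns per arm and no named term for follow-up length.

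**Conclusion.** The point holds as a conditional weakness that is inexpensive to close. Any difference between arms in mean follow-up length would pass into the programme coefficient, and no term named in the model would remove it. The bias is zero if timing was balanced. It is about 0.04 to 0.10 kg/m2 if mean follow-up differed by 1.5 months. That range rests on an assumed gap and an assumed natural BMI rise of 0.3 to 0.8 kg/m2 per year, neither of which is in the document. Whether any gap exists cannot be judged from the article; measurement dates by town would settle it.

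**What to change.** 1. Run the intermediate and final waves, which the article still describes as future work, in the same town and school order as baseline and at the same pace. Follow-up length is then equal across towns even if baseline dates were unbalanced. Pace matters as well as order: if a three-month baseline were followed by a one-month final wave in the same order, the 1.5-month gap would shrink only to 1.5 − 0.5 = 1.0 month.
2. Add elapsed time between the two measurements as a fixed effect in the model of the Statistic section, and tabulate measurement dates by town and arm.

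A comparison of autumn 2012 with autumn 2013, using the intermediate collection already planned in children, is optional as a sensitivity analysis. It covers only the first of the two years.

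The cost is minor scheduling work, one extra covariate and one table; no extra children are needed. The covariate needs the date of each measurement, which the article does not say is recorded. It cannot rescue the comparison if timing and group are fully aligned, so the first step carries most of the weight.

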### Statistic

Data clean-up will be performed to minimize errors. Linear multivariate mixed models will be fit to analyze differences in changes in quantitative variables between groups. Pre-post changes will be considered as the response variable, and participants’ (age, gender, etc.) and municipalities’ characteristics (group membership) will be included as fixed effects explanatory variables. Additionally, to account for the hierarchical structure of the data, municipalities (Terrassa, Sant Boi de Llobregat, Molins de Rei, and Gavà) will be added to the model as random effects factors.

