### Sample size calculation

The sample size calculation is based on data on 1 year changes in BMI of children from 14 towns where the THAO intervention program has been implemented. A decrease in BMI of 0.55 kg/m^2^ was observed. Therefore, we considered reasonable to assume a difference in BMI of 0,6 kg/m^2^ between control and intervention group. 1070 participants in each group are necessary to detect a difference in BMI of 0.6 kg/m^2^ or higher assuming a 0,05 alpha risk and 0,2 beta risk in a bilateral contrast. A BMI standard deviation of 4.43 kg/m^2^ was assumed and 20% of missing during follow up was estimated.

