### Intervention

The THAO-Child Health Program is being implemented in Terrassa and Sant Boi de Llobregat, with Molins de Rei and Gavà acting as control cities. Repeated measures of dietary intake and behaviour, physical activity, sleep quality, quality of life, and anthropometric variables will be performed during 2 years among all participating children. Additionally, parental sociodemographic variables, diet quality, and physical activity will be recorded. Computer-based software and questionnaires have been developed to record children’s lifestyle habits.

The main objective of the THAO-Child Health Program is the prevention of childhood obesity through the promotion of healthy lifestyles of children and their families. THAO-Child Health Program it’s leaded by the city council which appoints the local coordinator who is supported by a multidisciplinary local team to reach all key sectors (family, school, health professionals, sports, media, shops and market). It’s a complete multisetting and multistrategy CBI.The Thao Foundation coordinate networks which develop the public health strategy, create the graphic materials and activities to all local key sectors. Furthermore, it gives the initial and the periodical training to local teams and coordinators and provides a constant support and annual evaluation to each town involved. All actions are being communicated by multiple channels (Figure 1).

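### Children are measured at three waves, but the stated model takes one pre-post change per child, so the intermediate wave is unused and children without a final value do not contribute

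*Protocol article*

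**What the plan says.** Under Evaluation plan, children and parents are assessed at the start of the first school year and the end of the second. For children there is a third occasion: "An intermediate data collection at the beginning of the 2^nd^ scholar will be performed in children". The Intervention section likewise announces repeated measures that "will be performed during 2 years among all participating children".

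The Statistic section then fixes the model. For quantitative variables it is a linear mixed model in which "Pre-post changes will be considered as the response variable". Participant characteristics and group are fixed effects, and the four municipalities "will be added to the model as random effects factors". No wave term, group-by-wave term or child-level term is named.

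Under Sample size calculation, "20% of missing during follow up was estimated". Under Ethical issues, the data of a child are deleted automatically if the child or family leaves the study.

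**The concern.** A single pre-post change needs both the first and the last measurement. The middle measurement has no place in that response, and a child who lacks the last one has no response at all. The stated model is therefore a complete-case analysis of two of the three planned waves.

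It gives an unbiased group contrast if loss depends only on covariates in the model, including group. It may not if loss also depends on how the child's weight has developed, which is conceivable when the measurement is being weighed. The middle wave is the recorded evidence of that development. A likelihood model that includes it can condition on it; the change score cannot.

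The design also loses a time point that it has reason to want. The assumed effect comes from one-year BMI changes in 14 towns, and the start of year 2, about one year after the autumn 2012 baseline, is the only follow-up near that horizon.

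**Working it through.** **Inputs from the article.** Difference 0.6 kg/m²; SD 4.43 kg/m²; two-sided alpha 0.05; power 0.80; 20% missing; 1070 per group (all from Sample size calculation); 2249 recruited (Subjects).

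**Step 1: the plan's own figure.**
- n per group = 2(z₀.₉₇₅ + z₀.₈₀)² × SD² / difference² = 2 × (1.960 + 0.842)² × 4.43² / 0.6², which rounds up to 856.
- Allowing for loss: 856 / (1 − 0.20) = 1070, exactly as stated.

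The calculation thus treats the 20% as lost to the analysis, which agrees with a complete-case reading of the model.

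**Step 2: children without a final value at 20% missing.**
- Planned: 0.20 × 2140 = 428, leaving 1712.
- Recruited: 0.20 × 2249 = 449.8, about 450, leaving about 1799.

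Power on the article's inputs is 80.0% with 856 per group and 81.9% with 80% of 2249 (equal split assumed). Planned power is met without the middle wave.

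**Step 3: precision if all three waves are modelled.** The article gives neither the within-child correlations nor the share f of children missing the last visit who have the middle wave, so both are assumed and varied.
- Complete-case change score: variance of the contrast = 2 × SD² × (2 − 2ρ₁₃) / 856, where ρ₁₃ is the correlation between the first and last waves.
- Three-wave likelihood model: information per group I = Σ nₖ Zₖ′(ZₖVZₖ′)⁻¹Zₖ over three patterns out of 1070 (all waves 80%; waves 1 and 2 only 20% × f; wave 1 only 20% × (1 − f)). Variance = 2c′I⁻¹c with c = (−1, 0, 1).

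Example, AR(1) with correlation 0.90 and f = 1: ρ₁₃ = 0.81; complete-case SE = 4.43 × √0.38 × √(2/856) = 0.1320; three-wave SE = 0.1252; variance ratio 1.111; 856 × 1.111 ≈ 951 complete children per group.

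Variance ratio (equivalent complete children per group, against 856):

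| Assumed correlation | f = 0 | f = 0.5 | f = 1 |
|---|---|---|---|
| AR(1) 0.90 | 1.019 (873) | 1.068 (915) | 1.111 (951) |
| AR(1) 0.95 | 1.010 (864) | 1.064 (911) | 1.111 (951) |
| Compound symmetry 0.80 | 1.020 (873) | 1.041 (891) | 1.059 (906) |
| Compound symmetry 0.90 | 1.010 (865) | 1.035 (886) | 1.056 (904) |

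The complete-case variance is about 1 to 11% larger. The table ignores town clustering and assumes that every child missing the last visit keeps the earlier data. If all of them had withdrawn and been deleted, nothing would be left to recover and the gain would be nil.

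**The case against.** The Statistic section is a short paragraph in a journal article. Imputation, or a secondary analysis of the middle wave, may be in a fuller document, and its absence here is no fault. The same paragraph also serves the parents, who have only two assessments, so pre-post may be a loose summary. This stands in part: the article does not say that the middle wave will never be analysed. But it does fix the response and the random effects, and these do not fit three waves. Reading the plural as change to each follow-up wave does not help. Each child would then supply two correlated responses sharing one baseline, with only a town effect to account for it.

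A reader might infer that half of the roughly 450 children, about 225, could be brought back. The documents do not support that number. It assumes that half the loss falls after the middle wave and that none of those families withdrew. Neither share is given, and deletion on leaving lowers the number.

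A reader might also infer that the trial is underpowered or the group contrast biased. Neither follows. The sample size already allows for the 20%. Bias needs loss related to outcome beyond the modelled covariates and differing between groups, and nothing in the article shows this.

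Finally, with two towns per group, more measurements per child do not reduce between-town variance. Where that variance is present, the precision gain will be smaller than in the table.

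**Conclusion.** The point holds with a modest size. The stated model leaves one of the three child waves unused and excludes children without a final value, about 450 of 2249 if the expected 20% is right. How many could contribute under a three-wave model is unknown. The precision gain is about 1 to 11% of variance, given AR(1) correlations of 0.90 to 0.95 or compound symmetry of 0.80 to 0.90, no deletion among those missing the last visit, and no town clustering.

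Precision is the lesser reason to change. The better ones are that the analysis would rest on missing at random given the observed waves, and that an effect at about one year becomes estimable from data already planned. The change is worth making, but the stated sample size needs no correction on this account. The point concerns children only.

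**What to change.** For the children's quantitative outcomes, state that the values at all three waves are the response. Fixed effects are group, wave, group-by-wave and the planned participant covariates. Add a within-child covariance (or a child random effect) and retain the municipality term. Let the covariates and the municipality effect vary by wave: a constant effect on level cancels from a change and would not do the work it does in the planned change model.

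Name the group difference in change from baseline to the end of year 2 as the main contrast, and report the change to the start of year 2 beside it. Keep baseline as one of the responses. Using it as a covariate would still drop children with baseline only, and would alter the quantity estimated in a comparison of towns that are not described as randomised. Keep the complete-case change score as a sensitivity analysis, and report how many children missed the last visit and how many were deleted after withdrawal.

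The cost is wording and programming; no new data are needed. The downside is that a within-child covariance structure, and the form of the town term across waves, must be specified in advance.

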#### Online software

All lifestyle data are self-reported with the assistance of trained personnel. Dietary intake information based is collected by a new on-line program at each participant’s school. This program consists of a single and structured 24-h recall. Photographs were provided for all foods and beverages. Additionally, photographs of different portion sizes of most consumed foods of Spanish children aged 8 to 10 years are available.

The online program includes, beside the 24h recall, the following questionnaires

1. The KIDMED questionnaire [9]

2. The Dutch Eating Behaviour Questionnaire for Children (DEBQ-C) [10]

3. An eating habit questionnaire.

4. The Physical Activity Questionnaire for Children (PAQ-C) [11].

5. The KIDSCREEN-10 questionnaire [12]

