### Ethical issues

Parent consent was requested for each children and were performed parent meetings as requested by the schools. At any time the children or their family can leave the study and the data is automatically deleted.

The collection of anthropometric variables was performed in strict privacy conditions and gender dependent.

The study protocol was approved by the ethical committee of IMAS – Parc de Salut Mar, Barcelona, Spain.

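### The random effects stop at municipality: if the four-town variance is estimated at zero, no term carries school clustering and the programme test can reject too often

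*Protocol article*

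**What the plan says.** The Statistic section plans linear mixed models on each child's pre-post change. Group membership and participant characteristics are fixed effects. The statement on clustering is "Additionally, to account for the hierarchical structure of the data, municipalities (Terrassa, Sant Boi de Llobregat, Molins de Rei, and Gavà) will be added". The four towns are thus the only random factor, and no school or class term is named.

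Elsewhere the article shows that school is a real level of the data:
- Under Subjects, children are defined by elementary-school grade.
- Under Online software, dietary information "is collected by a new on-line program at each participant’s school". The same program carries the diet-quality, eating-behaviour, physical-activity and quality-of-life questionnaires.
- Under Ethical issues, parent meetings "were performed parent meetings as requested by the schools".

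The programme is allocated by town: "The Thao-Child Health Program was implemented in Terrassa y Sant Boi de Llobregat whereas Molins de Rei and Gavà serve as control cities".

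**The concern.** The model is said to deal with the hierarchy, but it contains only the top level. Changes in children from the same school may be correlated, and the only term that can pick this up for the programme contrast is the town variance. That variance rests on four towns, two per group, so it is poorly estimated and may come out at zero. The fitted model then treats all children as independent given the fixed effects, and the standard error of the programme effect is too small in exactly those analyses. At stake is a false claim that the programme works on BMI change or on any lifestyle outcome analysed the same way.

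**Working it through.** **The plan's own figure.** Inputs from Sample size calculation: difference 0.6 kg/m², SD 4.43 kg/m², two-sided alpha 0.05, power 80%, 20% loss.

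n = 2 × (1.960 + 0.842)² × 4.43² / 0.6² = 855.7, rounded up to 856; 856 / 0.8 = 1070 per group. This matches exactly and contains no design effect, so clustering is not allowed for there either.

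**Assumed inputs.** The article gives no school count and no ICC. I take 10 schools per town and 45 children per school: 4 × 10 × 45 = 1800, close to 2249 × 0.8 = 1799. School ICC is 0.01, 0.02 or 0.05; town ICC is 0 at first. Total variance is 1 and the design is balanced.

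**Step 1: true standard error.** With two towns per group, the variance of the programme contrast equals the variance of one town mean:

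V = town variance + school variance / 10 + child variance / 450.

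At school ICC 0.02: V = 0.02/10 + 0.98/450 = 0.00418, so SE = 0.065. Under independence, SE = √(1/450) = 0.047.

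**Step 2: when the town term suffices.** The between-town mean square has expectation B = 450 × V. A positive town-variance estimate means that the SE comes from this mean square, which already contains the school component. In a balanced design the SE is then the same with or without a school term, provided the larger model's town variance is also positive.

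**Step 3: how often the town variance is set to zero.** This happens when the between-town mean square (2 df) falls below the pooled within-town mean square W. A chi-square on 2 df divided by 2 is exponential, so P(zero) ≈ 1 − exp(−W/B). The SE in those trials relative to the true SE is about √(W/B).

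| School ICC | B | W | P(zero) | SE if zero / true SE |
|---|---|---|---|---|
| 0.01 | 1.44 | 0.999 | 50% | 0.83 |
| 0.02 | 1.88 | 0.998 | 41% | 0.73 |
| 0.05 | 3.20 | 0.995 | 27% | 0.56 |

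**Step 4: type I error.** Simulation with no programme effect, rejecting when |z| > 1.96:

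| School ICC | Town ICC | Town only | Town + school |
|---|---|---|---|
| 0.01 | 0 | 6.8% | 4.2% |
| 0.02 | 0 | 9.0% | 4.3% |
| 0.05 | 0 | 13.0% | 4.3% |
| 0.02 | 0.002 | 12.1% | 7.4% |
| 0.02 | 0.02 | 17.6% | 16.1% |

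With 560 children per town in 5, 10 or 20 schools and no town variance, the range at school ICC 0.01 to 0.05 is 5.5% to 16.5% (town only) against 3.8% to 5.1% (town + school). The town variance is set to zero in 14% to 54% of runs.

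**Step 5: why the last row barely improves.** At town ICC 0.02, B = 450 × 0.02 + 0.96 + 45 × 0.02 = 10.86, and P(zero) is only about 9%. The excess there comes from using a normal reference for a variance on 2 df: P(|t₂| > 1.96) = 1 − 1.96/√(2 + 1.96²) = 18.9%. With the 2-df critical value of 4.30, both models stay below 5% in every setting run.

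**The case against.** A reader might infer that school clustering simply stays in the residual and that standard errors are too small throughout. The documents do not support this. The programme is allocated by town and a town effect is fitted, which is a recognised way to handle lower-level clustering. Averaged over replicates, the root-mean-square town-only SE was never below the true one: with 10 schools per town, 56 children per school and school ICC 0.02 it was 0.064 against 0.061. The shortfall is confined to analyses with town variance at or near zero. That part of the objection stands.

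The inflation also depends on a large-sample reference. The article names no reference distribution, and a 2-df t reference controls type I error without a school term. This stands too. It is why the fix pairs the two changes, and why the school term alone is not enough when towns truly differ.

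That children were sampled through schools is an inference. The article describes recruitment from four cities, gives no school sampling scheme, and does not say where anthropometry was done. Nesting in schools does not depend on that: the children are elementary-school pupils, and the online data are collected at their schools.

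A reader might also infer understated standard errors for covariates that cluster by school. The article names only age and gender as participant covariates and states no aim of inference on covariates, so the point does not rest on this.

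Finally, a fuller plan may list more levels. But the article does more than stay silent: it gives the model's purpose and lists the random factor meant to meet it, and school is not there.

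**Conclusion.** The point holds in a limited form. The stated hierarchy is incomplete. For the programme effect this matters when the four-town variance is estimated at or near zero, which is common if towns differ little. Under the assumed 10 schools of 45 children per town and no true town variance, that occurs in 27% to 50% of trials. Over all trials, type I error with a large-sample test is then about 7% to 13%, against about 4% with a school term. As town variance grows the gain shrinks, to 17.6% against 16.1% at town ICC 0.02, and the small number of towns becomes the main problem. These sizes rest on assumed school numbers and ICCs of change scores, a balanced design and a normal reference. The change is worth making, but it does not by itself secure the test.

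**What to change.** In the Statistic section, add a random intercept for school nested in municipality and keep the municipality effect, for every outcome model. State that the programme effect is tested with small-sample degrees of freedom based on the number of towns (4 towns less 2 group means, so 2). Report the estimated school and town ICCs with the results.

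The cost is one more model term and a more conservative test. School should already be known for each child, because the online data are collected there. The 2-df critical value is 4.30 instead of 1.96, so power falls, and the test is very conservative if towns do not differ (about 0.1% rejection in the town-only model with 56 children per school and school ICC 0.02). That loss follows from having four towns, and adding a school term does not remove it.
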